**Fig. 2 Fig2:**
[figure not shown]
An example frame from the screen-based eye-tracking stimuli. The image is displayed with permission from the actress

#### Screen-based eye-tracking data analysis

The screen-based eye-tracking data will be analyzed using in-house R scripts. The fixations will be extracted using the I2MC toolbox [60]. We will measure the total looking time to three Areas-of-Interest (AOIs): (a) the entire face oval, (b) the eyes, (c) the mouth. The eyes and the mouth AOIs will have a comparable surface area size. Then, the proportion of total looking time (PTLT) for each AOI (mouth vs. eyes) relative to the total looking time to the whole face will be calculated, producing two variables: the ratio of looking time for the eyes compared to the face (PTLT Eyes: Eyes-to-Face Ratio), and similarly for the mouth (PTLT Mouth: Mouth-to-Face Ratio).

### Objective 3. To investigate how the transition to independent sitting associates with infants’ vocal production

Recording of infant-parent interaction from each testing session will be coded offline to annotate infants’ vocalizations using PRAAT software (Boersma and Weenink, 2025, https://www.fon.hum.uva.nl/praat/. The coders will mark the onsets and offsets of each vocalization at the utterance level. An utterance is defined as a vocalization occurring on one expiration cycle [61, 62]. All vocalizations will classified into four distinct, non-overlapping categories (based on [63]): (a) reflexive sounds (laugh and cry), (b) protophones (squeals, vowel-like sounds, growls, whispers, yells, grunts), (c) syllables. The rate per minute, total duration of vocalizing and the mean duration of vocalization will be analyzed.

### Control variables

#### Chronological age and socioeconomic variables

We will use the infant’s chronological age at each testing session as a control variable. Furthermore, we will collect information on the family’s socio-economic status, the infant’s health, the course of pregnancy, and risk factors during the first testing session through a structured interview with the caregiver.

#### Questionnaire data

**Infant Behavior Questionnaire (Very Short Version)**: Measures infant temperament based on caregiver reports (IBQ-R [64, 65]; Polish adaptation by [66]).**Language Use Inventory (only Part A: Gestures)**: Evaluates early language development by assessing a child’s use of gestures as a precursor to verbal communication ( [67]; Polish adaptation by [68]).**Early Motor Questionnaire**: Assesses early motor development in infants and young children by evaluating gross motor, fine motor, and action/perception skills based on caregiver reports ( [69]; Polish adaptation by [70]).**Parental Beliefs on Motor Development & Motor Habits**: Examines parental attitudes and beliefs regarding children’s motor development and their influence on physical activity and motor habits [71].

Furthermore, given the link between parental mental health and its effects on infant developmental trajectories, with anxiety, depressive symptoms, and stress often having lasting effects on developmental trajectories [72], we decided to also include some control measures of parental mental health. Maternal mental health problems, even in non-clinical samples, have also been shown to influence motor development [73, 74] and are associated with the dynamic organization of infant limb movement [75]. It could potentially relate to how mothers structure their infants’ proximal environment and constrain (or not constrain) their spontaneous movements. They could encourage or discourage the infant’s movement through space (e.g., through the use of devices such as baby bouncers) and provide more or fewer opportunities for their exploration of the environment (e.g [74]).

**Edinburgh Postnatal Depression Scale**: Screens for symptoms of postnatal depression in parents, focusing on emotional well-being and depressive symptoms [76].**State/Trait Anxiety Inventory**: Assesses both temporary (state) and chronic (trait) anxiety levels in parents, distinguishing situational distress from general anxiety tendencies ( [77], Polish adaptation by [78]).**Parental Burnout Assessment Questionnaire**: Measures the extent of parental burnout, characterized by exhaustion, emotional distancing, and loss of fulfillment in the parenting role ( [79], Polish adaptation by [80]).

### Measurement of sitting capacity and sitting performance

Following the World Health Organization’s International Classification of Functioning, Disability, and Health (2001) and the approach proposed by Kretch et al. [81], we will differentiate between *sitting capacity* – the potential to perform a task in a standardized or idealized setting – and *sitting performance*, which reflects the actual execution of the task in a natural, everyday environment. Infant’s capacity for sitting will be assessed through the Alberta Infant Motor Scale (AIMS [56]), whereas their *performance* will be evaluated by observing how they sit during dyadic interactions. Thus, the *sitting capacity* represents the ability to carry out a skill under controlled or prompted conditions, while *sitting performance* indicates the unprompted application of that skill in real-world contexts.

### Measurement of *sitting capacity*

To assess infants’ stage of sitting acquisition, we will use the Alberta Infant Motor Scale (AIMS [56]), which is an observational assessment tool for measuring motor development of infants aged 0 to 18 months. It consists of 4 subscales that list skills in four body positions: prone, supine, sit, and stand. For each of the four positions, an experimenter needs to identify and score the least and most advanced items observed during the assessment. The items between the least and most advanced of the observed items represent the infant’s possible motor repertoire in that position, also considered their “window” of current skills. Each item within this window is then scored as either “observed” or “not observed” by the experimenter. All of the “observed” scores on a given subscale are then summed to obtain a positional score. Finally, all positional scores are summed to obtain a total AIMS score. In the planned analyses, we will use both the “sitting” score and the total score to assign infants to one of the three levels regarding sitting experience (pre-sitting, transition, expert).

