### Measurement of *sitting performance*

To further confirm infants’ stage of sitting acquisition, we will also analyze the actual time that infants spend in each posture during each parent-child interaction task. Following the previously established procedure [57], we will use the machine-learning classifier (CatBoost) on data recorded with Inertial Motion Units (consisting of accelerometers, magnetometers, and gyroscopes) worn by infants on arms and legs. Inertial Motion Units (MTw Awinda, Xsens Technologies B.V.) connected wirelessly through an Awinda station receiver (Xsens Technologies B.V.) and synchronized in real-time with MT Manager Software (Xsens Technologies B.V.) were recording at 60 Hz. We will specifically focus on the % of the recording time that the infant spent in an independent sitting position, that is, excluding episodes of supported sitting.

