### Statistical analyses

Data will be analyzed according to the aims of the study. The use of multiple eye-tracking methods in a single study may increase the risk of data attrition. Hence, we will adopt a flexible policy of participant inclusion on an analysis-by-analysis basis to maximize the sample size for each type of modeling. Thus, linear mixed models will be used to measure the effect of sitting expertise on each outcome variable. These models are suitable for longitudinal designs such as ours and for dealing with potential missing data. Infants’ age will be added to the analyses to control for the interaction between age-related and motor-development-related effects. The linear mixed models take into account the dependency and ordering of the data within subjects in repeated-measures designs. Moreover, even if a subject is missing one or more of the repeated measurements, the remaining data of that subject are used in the analysis.

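### Sitting level, the exposure in every model, is assigned partly from the AIMS total score, so non-sitting skills can move infants between levels and mix general motor maturity into the sitting effect

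*Protocol article*

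**What the plan says.** All references are to the protocol article.

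- **Measurement of sitting capacity** describes the AIMS: "It consists of 4 subscales that list skills in four body positions: prone, supine, sit, and stand". Each position yields a positional score, and "all positional scores are summed to obtain a total AIMS score". The planned analyses will then use the sitting "score and the total score to assign infants to one of the three levels regarding sitting experience": pre-sitting, transition or expert. The article does not say how the two scores are combined.
- **Statistical analyses** makes that level the exposure throughout: "linear mixed models will be used to measure the effect of sitting expertise on each outcome variable". Age is the only added term named there.
- **Tracking developmental transitions of multiple skills** gives the purpose: to centre cross-domain effects on one particular motor milestone and so separate age-driven from posture-driven effects.
- **Study design** says the AIMS is there to measure capacity to sit alone. It defines the attempting and expert stages by sitting ability, but the pre-sitting stage by a prone skill.
- **Measurement of sitting performance** adds motion-sensor posture data as a further confirmation of stage: "we will also analyze the actual time that infants spend in each posture during each parent-child interaction task".

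**The concern.** Three of the four AIMS positions are not sitting. Once the total helps decide the level, skill in prone, supine or standing can shift an infant across a boundary with no difference in sitting. Part of any contrast between levels then reflects how advanced the infant is in general.

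The protocol's own background shows why this matters. The section on sitting in relation to visual attention and vocal production reports that gross motor skill in general is linked to prelinguistic and social development, which lie close to the outcomes here. It also cites a sitting association with later receptive language that held after control for overall gross motor development. The protocol thus treats general motor level as something to separate from sitting, and then builds it into the exposure. A positive result for any of the three objectives would be open to the reading that more mature infants, rather than better sitters, look or vocalise differently.

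**Working it through.** **1. Is this a stated rule or an omission?** It is stated: both scores are used to assign level. A fuller analysis plan could supply cut-offs, but it could not keep this rule and also keep non-sitting skill out of the assignment.

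**2. Does anything else in the plan remove the problem?**

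- Age adjustment does not. Infants of the same age differ in motor skill, and that difference is what the total brings in.
- The Early Motor Questionnaire, a general motor measure, is listed under Control variables, but no use of it in the models is stated.
- Confirmation by motion sensors comes with no rule for resolving disagreement with the AIMS.

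**3. How large could it be?** The plan gives no figure on this point, and its minimum of about 30 participants does not enter. The following is an illustration; every input is an assumption.

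Let S be sitting skill and O other-posture skill, each with SD 1 and correlation r. Levels are thirds of X = S + wO, where w is the weight that non-sitting skill receives. With equal spreads, adding the sitting score to the total gives S + (S + O) = 2S + O, that is w = 0.5. The total alone gives w = 1. A larger w stands for non-sitting subscales that dominate the total.

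The means of the top and bottom thirds of a normal variable differ by 2.18 SD. The differences between top and bottom levels are then:

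- in sitting skill: 2.18 × (1 + wr) / √(1 + w² + 2wr)
- in the part of O independent of S: 2.18 × w√(1 − r²) / √(1 + w² + 2wr)

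Example with r = 0.5 and w = 1: the denominator is √3 = 1.732. Sitting: 2.18 × 1.5 / 1.732 = 1.89. Independent part: 2.18 × 0.866 / 1.732 = 1.09.

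A simulation of 400,000 infants agrees and also gives the share who change level relative to a sitting-only rule:

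| w | r | Change level | Sitting (SD) | Non-sitting skill independent of sitting (SD) |
|---|---|---|---|---|
| 0 (sitting only) | 0.3 to 0.9 | 0% | about 2.2 | 0 |
| 0.5 | 0.3 | 23% | 2.01 | 0.84 |
| 0.5 | 0.9 | 9% | 2.16 | 0.33 |
| 1 | 0.3 | 35% | 1.75 | 1.29 |
| 1 | 0.5 | 29% | 1.89 | 1.09 |
| 1 | 0.9 | 13% | 2.13 | 0.49 |
| 3 | 0.3 | 49% | 1.20 | 1.82 |
| 3 | 0.9 | 20% | 2.06 | 0.73 |

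**4. Reading the table.** The contrast between levels still carries sitting skill in every row, but it also carries a difference in unrelated motor skill that a sitting-only rule would not create. The zero in the first row covers only the part of O independent of S. The shared part still differs between levels: with r = 0.5, O as a whole differs by 0.5 × 2.18 = 1.09 SD even under a sitting-only rule. Changing the assignment rule removes the added contamination; the shared part needs a covariate.

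The illustration is cross-sectional and cuts levels into thirds. The study follows each infant over 3 or 4 ordered visits timed by parent reports, so the table shows direction and rough scale and is not an estimate for this trial.

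**The case against.** The strongest reply is that the sitting score is used as well, the total itself contains the sitting items, visits are timed around the transition to independent sitting, and two of the three stages are defined by sitting. This stands against the inference that the sitting effect simply turns into a general-motor-maturity effect. The documents support a mixture of unknown proportion, not a replacement.

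A second reply is that the protocol's staging does need non-sitting information, because pre-sitting is defined by a prone skill. That also stands, and a rule based only on sitting items must deal with it. It does not justify the total score, which brings in supine and standing skills and applies at all three levels.

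Three further inferences are tempting but unsupported:

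- **Scoring within the window.** Read literally, observed "scores on a given subscale are then summed to obtain a positional score", so items below the window might seem to earn nothing. The sentence is a short paraphrase of a cited, standardised instrument, and its scoring manual is not at hand. It cannot be taken as the operating rule.
- **Motion-sensor data overriding stage.** The text says confirm, and states no override. It describes performance as something "which reflects the actual execution of the task in a natural, everyday environment", distinct from capacity. The screen task for Objective 2 also takes place on the caregiver's lap before the wearables are fitted.
- **A specific loss of sample size.** A symmetric 15% swap between two levels would give 1/0.70² = 2.04 times the N, but no swap rate has a source in the documents. The formula assumes error unrelated to the outcome, which is doubtful here, and does not fit ordered visits within an infant.

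**Conclusion.** The point holds as a defect in how the exposure is defined. The plan commits to using a score that includes prone, supine and standing skills to assign sitting level, that level is the exposure for every outcome, and age does not correct for it. This conflicts with the stated aim of isolating one milestone.

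The degree of mixing cannot be derived from the documents, because neither the combination rule nor the correlation between postures is given. Under the assumptions above with equal weights, the unwanted difference between top and bottom levels is 0.49 to 1.29 SD of motor skill unrelated to sitting. At the lower weight of 0.5 it is 0.33 to 0.84 SD. Whether it biases a given outcome depends on how far that outcome follows general motor skill, which the protocol's background suggests for vocal and social measures.

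**What to change.** - Assign level from the AIMS sitting items or sitting score by a rule written down before analysis, and drop the total score from the assignment.
- Reconcile this with the prone-based pre-sitting definition in Study design. For example, keep the prone criterion for scheduling the first visit, and define the pre-sitting level for analysis by the absence of independent sitting.
- Add the non-sitting AIMS remainder (total minus sitting score) as a covariate in a sensitivity model for each outcome.
- Keep the percentage of time in independent sitting from the motion sensors as a separate performance measure, in line with the article's own distinction between capacity and performance.

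The cost is a few sentences of text and a re-derivation from data already being collected. The section The current study says that data analysis has not started, so the change can still be made in advance. The drawback is some extra analysis and lower precision in the sensitivity model, because the remainder is correlated with sitting.

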### Measurement of *sitting performance*

To further confirm infants’ stage of sitting acquisition, we will also analyze the actual time that infants spend in each posture during each parent-child interaction task. Following the previously established procedure [57], we will use the machine-learning classifier (CatBoost) on data recorded with Inertial Motion Units (consisting of accelerometers, magnetometers, and gyroscopes) worn by infants on arms and legs. Inertial Motion Units (MTw Awinda, Xsens Technologies B.V.) connected wirelessly through an Awinda station receiver (Xsens Technologies B.V.) and synchronized in real-time with MT Manager Software (Xsens Technologies B.V.) were recording at 60 Hz. We will specifically focus on the % of the recording time that the infant spent in an independent sitting position, that is, excluding episodes of supported sitting.

### Statistical analyses

Data will be analyzed according to the aims of the study. The use of multiple eye-tracking methods in a single study may increase the risk of data attrition. Hence, we will adopt a flexible policy of participant inclusion on an analysis-by-analysis basis to maximize the sample size for each type of modeling. Thus, linear mixed models will be used to measure the effect of sitting expertise on each outcome variable. These models are suitable for longitudinal designs such as ours and for dealing with potential missing data. Infants’ age will be added to the analyses to control for the interaction between age-related and motor-development-related effects. The linear mixed models take into account the dependency and ordering of the data within subjects in repeated-measures designs. Moreover, even if a subject is missing one or more of the repeated measurements, the remaining data of that subject are used in the analysis.

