### Acquisition of sitting skills in relation to visual attention and vocal production

One of the key gross motor achievements changing the visual perspective of young infants is the developmental ability to sit independently [12, 13]. Infants usually start sitting independently between 5 and 8 months of age, with large disparities in the time of its onset (WHO Motor Development Study [14]). While sitting, infants are more likely to have toys in their view [12, 15], and they are also more in the center of their field of view [12, 16]. Similarly, sitting infants are more likely to see a caregiver’s face [15, 17], and the episodes of parent-infant mutual gaze and joint attention also happen more often when infants sit [17]. The caregivers are more likely to provide opportunities for learning when infants are sitting independently than when they are in other positions [13]. Interestingly, there are differences in how caregivers play with infants depending on their sitting proficiency. Supported sitting provides infants less of a boost to cognitive opportunities than independent sitting, potentially due to the fact that when caregivers provide postural support, they are likely to be positioned behind their infants, decreasing chances for face-to-face engagement and joint attention [13]. Accessibility of important social information from caregivers’ faces is easier during face-to-face play than during supported sitting [18].

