Sitting has since long been postulated to relate to advances in vocal development. Yingling [19] documented significant associations between the onset of unsupported sitting and advances in consonant-vowel vocalizations in the first year of life, which are important precursors to speaking first words. Gallen et al. [20] reported that more advanced gross motor skills are linked to more advanced prelinguistic development and social development. Similarly, positive associations between gross motor and communication development were found in very preterm infants, with higher expressive language scores and more vocal production characterizing infants mastering unsupported sitting [21]. Furthermore, the earlier-than-average development of sitting skills (from 3 to 5 months of age) was predictive of subsequent higher receptive language scores at later time points (at 10 and 14 months of age), even while controlling for overall gross motor development [22]. However, it is unknown whether the acquisition of independent sitting skills is related to advances in infants’ vocal production.

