### Tracking developmental transitions of multiple skills

As each new posture is initially unstable (as measured behaviorally or kinematically) and requires practice (involving multiple failed attempts), it is important to track changes across the process of learning a new motor skill. For example, expert-sitters can adapt their postural control to maintain balance on both compliant and firm surfaces [47], but similar variability can be difficult for infants who just started to sit independently (new-sitters). For them, the challenge of staying upright takes a lot of attentional resources, minimizing their engagement in other behaviors, such as reaching for objects [48, 49]. New-sitters, during their first attempts, need to learn how to maintain their balance to avoid falling and adjust the coordination of the upper limbs with the demands of sitting upright (e.g [37]).,. Once the novel skill is mastered, it requires less attentional resources and allows for the simultaneous performance of other actions [50]. Thus, behavioral flexibility increases with sitting experience [51].

In this study, we align the testing schedule with the onset of independent, arms-free sitting rather than chronological age in order to explore how visual attention and vocal production change across the process of learning a new motor skill. We will control for chronological age, but the milestone-based approach aims to account for individual differences in the timing of sitting acquisition. Recently, Gallen et al. [20] showed that age-adjusted relative advances in motor development are linked to concurrent prelinguistic and social development, supporting the idea of developmental interaction across neurocognitive domains. In this study, we aim to capture such developmental interactions across neurocognitive domains but center them around a specific motor milestone to better understand the age-driven vs. posture-driven effects.

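### A single age-at-visit covariate separates age from sitting stage only if within-infant and between-infant age slopes are equal; report a model that splits age beside it

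*Protocol article*

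**What the plan says.** Under Statistical analyses, "linear mixed models will be used to measure the effect of sitting expertise on each outcome variable", and infants' "age will be added to the analyses to control for the interaction between age-related and motor-development-related effects". The section Chronological age and socioeconomic variables says which age is meant: the plan uses "chronological age at each testing session as a control variable". No term for onset age, infant mean age or within-infant age is named.

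The visits follow the milestone. In the section Tracking developmental transitions of multiple skills the authors write that "we align the testing schedule with the onset of independent, arms-free sitting rather than chronological age", and they state the inferential aim there: to "center them around a specific motor milestone to better understand the age-driven vs. posture-driven effects".

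The background section on visual attention and vocal production gives the spread of onset: "Infants usually start sitting independently between 5 and 8 months of age, with large disparities in the time of its onset". It also reports that "earlier-than-average development of sitting skills (from 3 to 5 months of age) was predictive of subsequent higher receptive language scores". The section on tracking transitions adds that infants who are motor-advanced for their age are ahead in prelinguistic and social development.

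**The concern.** Age at a visit is the infant's onset age plus the time from onset to that visit. Stage already accounts for most of the second part. Once stage is in the model, most of the remaining age variation lies between infants: within a stage, the older infants are the later sitters. The age coefficient then reflects two things, growth within an infant and the difference between early and late sitters. It stands for maturation only if the two slopes agree.

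If late sitters score lower for their age, the between-infant slope lies below the within-infant slope. The fitted coefficient then understates maturation, and the remainder goes into the stage contrast as an apparent gain from pre-sitting to expert-sitting. Objectives 1 and 3 predict a gain of that kind, and Objective 2 predicts a gradual rise, so the error would look like confirmation. At stake is the statement that a change is posture-driven rather than age-driven.

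**Working it through.** **The plan's own figure.** The Sample size section gives about 30 infants for a moderate effect in a repeated-measures design. Alpha, power and correlation are not stated. With noncentrality λ = f²·n·m·ε/(1 − ρ), and assuming f = 0.25, α = 0.05, ρ = 0.5, ε = 1 and m = 3, n = 28 gives λ = 0.0625 × 28 × 3 / 0.5 = 10.5 and 80% power; n = 31 gives 85%. The figure reproduces. It contains no age term, so it does not speak to the precision of an age-adjusted stage effect.

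**Form of the bias.** Let βW be the within-infant age slope, βB the between-infant slope, b the single fitted age slope (a weighted mix of the two) and D the mean age gap from pre-sitting to expert-sitting. The false expert-minus-pre effect is about (βW − b) × D. As the gaps between visits become uniform across infants, b tends to βB and the bias to (βW − βB) × D.

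**Inputs.** From the article: three stages, a target of 60 infants, onset at 5 to 8 months. Assumed: onset SD 0.75 month (3-month range / 4), with 0.5 and 1.0 also run; mean gap 1 month per stage (D = 2) with SD 0.25 or 0.5; intraclass correlation (ICC) 0.3 to 0.7; total SD 1; βW = 0.3 SD per month; true stage effect zero. Each setting had 1,500 runs of a random-intercept model. The rejection rate is for the joint stage test.

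**Results**, 60 infants, onset SD 0.75, gap SD 0.5, ICC 0.5:

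| βB | Single age: false effect | Rejection | Onset age added: false effect | Rejection |
|---|---|---|---|---|
| 0.3 (equal) | −0.01 SD | 5.0% | −0.01 SD | 5.7% |
| 0.2 | +0.11 SD | 6.7% | −0.01 SD | 6.1% |
| 0.0 | +0.32 SD | 19% | −0.01 SD | 4.9% |
| −0.3 | +0.66 SD | 61% | 0.00 SD | 4.8% |

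Other settings with βB = 0:
- Onset SD 1.0, ICC 0.5: +0.44 SD and 41% (gap SD 0.5), or +0.54 SD and 50% (gap SD 0.25).
- Onset SD 0.5, gap SD 0.5: +0.16 SD and 8% (ICC 0.7), or +0.34 SD and 15% (ICC 0.3).

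The formula agrees. At onset SD 1.0 the mean fitted slope was 0.085 (gap SD 0.5) or 0.032 (gap SD 0.25), so (0.3 − 0.085) × 2 = 0.43 and (0.3 − 0.032) × 2 = 0.54. The size depends on the difference between the slopes, and the sign can reverse: βW = 0 with βB = 0.3 gave −0.44 SD.

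**Literal reading of the word interaction.** Adding stage-by-age terms (age centred) does not repair it. At onset SD 0.75 and βB = 0 the false effect is +0.31 SD with 18% rejection.

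**Precision after the split.** Splitting age, like adding onset age, brings mean bias to about zero and the type I error to about 5%. The standard error of expert minus pre at 60 infants changes as follows:
- Onset SD 0.75, gap SD 0.5 (onset age added): 0.249 to 0.345, ratio 1.4.
- Onset SD 1.0, gap SD 0.5: 0.220 to 0.363, ratio 1.65.
- Onset SD 1.0, gap SD 0.25: 0.238 to 0.651, ratio 2.7.
- Mildest setting (onset SD 0.5, ICC 0.7): 0.246 to 0.282, ratio 1.15.

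At onset SD 1.0, power for a true 0.5 SD contrast falls from 62% to 28% (gap SD 0.5) or from 57% to 12% (gap SD 0.25).

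**How well the slopes can be compared.** In the split model the contrast variance is about 2σ²/n + D²·Var(βW estimate), with 2 × 0.5 / 60 = 0.0167. The standard error of the within-infant slope is then √[(0.363² − 0.0167)/4] = 0.17 (gap SD 0.5) or √[(0.651² − 0.0167)/4] = 0.32 (gap SD 0.25). A slope difference of 0.3 is therefore at most 1.8 or 0.9 standard errors.

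**The case against.** The strongest reply is that the article gives no model formula. It states no random-effects structure and no centring, and a fuller plan could already split age. That stands against two stronger readings. A reader might infer that age will be entered uncentred, so that stage effects refer to age zero; the text does not say so. A reader might also infer that the planned analysis is biased outright. It is not when the slopes are equal, and the bias is small when they are close.

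The background support is indirect. The receptive-language finding concerns 10 and 14 months, an outcome not measured here. The link between motor advance and prelinguistic level could itself be a stage effect, which the planned model would represent. Nothing cited shows an effect of onset timing on looking at faces, toys or mouths. The premise is therefore strongest for Objective 3 and weak for Objectives 1 and 2.

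It might also be inferred that every predicted stage effect could be spurious. The dip at attempting-sitting in Objectives 1 and 3 could not be: leftover maturation rises from stage to stage and works against a dip.

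Finally, replacing the single-age model would be a bias-variance choice, not a plain correction. Another set of runs (stage step 1.25 months, onset SD 1.0, late sitters lower by 0.15 to 0.30 SD per month of later onset) gave bias 0.29 to 0.57 SD and a standard error of 0.27, against 0.52 after the split. Root mean squared error for the single-age model is √(0.29² + 0.27²) = 0.40 at the low end, better than 0.52, and √(0.57² + 0.27²) = 0.63 at the high end, which is worse. That argues for keeping both models.

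What survives is that the article names one age variable and one aim, and that variable meets the aim only under an equality which is neither stated nor checked.

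**Conclusion.** The point holds as a conditional one. In this milestone-aligned design the planned age adjustment distinguishes age from posture only if within-infant and between-infant age slopes are equal, and the article's own background makes that doubtful, mainly for vocal outcomes. Under the assumptions above, the false expert-minus-pre effect runs from about 0.1 SD with 7% type I error to more than 0.5 SD with more than 50%. The slopes, onset spread, gap spread and ICC are all assumed, so the range shows what is possible and does not predict the study's result. The direction favours the hypotheses only if late sitters score lower for their age.

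**What to change.** Keep the planned single-age model. Beside it, fit and report a model with two age terms: infant mean age (or onset age dated from the weekly parent surveys) and the within-infant deviation at each visit. Report the difference between the two slopes with its interval. A non-significant difference should not be read as equality, because the comparison is imprecise.

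Describe a stage effect as posture-driven rather than age-driven only if the split model's estimate supports it. Otherwise report it as change aligned with the milestone that cannot be separated from age.

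No new data are needed: the surveys are already collected, and the article states that analysis has not started. The cost is the loss of precision shown above. At the planned sample size the study may be unable to separate age from posture, and the report should say so if that is the outcome. The split model also still assumes linear maturation, and that the spacing of an infant's visits is not itself related to the outcome.
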